# Efficacy and safety of Tibetan medicine Qingpeng ointment for acute gouty arthritis: protocol for a multi-center, randomized, double-blind, placebo-controlled trial

**DOI:** 10.1186/s13063-022-06338-1

**Published:** 2022-05-12

**Keywords:** Gout, Acute gouty arthritis, Joint pain, Qingpeng ointment, Tibetan medicine, Randomized controlled trial

## Abstract

**Background:**

Acute gouty arthritis (AGA) is an inflammatory arthritis clinically characterized by severe pain, swelling, and restricted movement of joints, which may cause physical disability and decrease quality of life. The use of recommended first-line treatment agents for AGA may be limited by adverse events. There has been a traditional use of alternative therapies for AGA. Tibetan medicine Qingpeng ointment is one of the on-market herbal products used for symptom relief of AGA. Previous clinical studies indicated that Qingpeng ointment can relieve pain, swelling, redness, and dysfunction of joints in patients with AGA. However, there is no rigorous randomized trial to demonstrate its benefit for AGA. In order to evaluate the efficacy and safety of Qingpeng ointment for AGA, we designed a randomized controlled trial.

**Methods:**

This study is designed as a multi-center, randomized, double-blind, placebo-controlled trial. Two hundred and six adults with acute flare of gout, and visual analogue scale (VAS) score of joint pain ≥ 3 points will be recruited. Participants will be randomly assigned to herbal treatment or placebo group at a ratio of 1:1. Qingpeng ointment, or equal placebo ointment, will be applied topically at involved joints twice a day for consecutive 7 days. Patients in both groups would be allowed giving diclofenac sodium sustained-release tablets as rescue therapy when VAS score of joint pain ≥ 7 points during the treatment. The primary outcomes will be joint pain measured by VAS score, and joint swelling measured using width and thickness of affected joints and VAS score. Other outcome measures will be joint mobility, joint redness, C-reactive protein, serum uric acid, and the use of rescue medicine as well as adverse effect.

**Discussion:**

To the best of our knowledge, this study is the first multi-center, randomized, double-blind, and placebo-controlled clinical trial to assess the efficacy of Tibetan medicine Qingpeng ointment for AGA. The findings of this study would provide evidence for its use to relieve symptoms of AGA.

**Trial registration:**

ISRCTN ISRCTN34355813. Registered on 25 January 2021

**Supplementary Information:**

The online version contains supplementary material available at 10.1186/s13063-022-06338-1.

## Background

Gout is an inflammatory arthritis occurring in response to monosodium urate crystals formation. It has been recognized as the most common form of inflammatory arthritis [1], with a prevalence of 1.1 to 3.9% [2–6]. The disease burden of gout is rising globally [7]. Acute gouty arthritis (AGA) is clinically characterized by severe pain, redness and swelling of joints, and restricted movement, which may cause physical disability, as well as decreased quality of life [8]. Colchicine, nonsteroidal anti-inflammatory drugs (NSAIDs), and glucocorticoids are recommended as first-line treatment agents for AGA [9, 10]. However, comorbidities that may result in contraindications to these drugs are common in patients with gout [11]. Moreover, the use of these drugs may be limited by adverse events. For example, colchicine can increase the rate of diarrhea and gastrointestinal adverse events when compared with placebo and active comparators [12]. NSAIDs are associated with increased risk of gastrointestinal bleeding [13] and may exacerbate renal failure [14]. Glucocorticoids may cause weight gain, cardiovascular disease, diabetes, and infections [15]. Therefore, a complementary and alternative therapy that can effectively alleviate the symptoms of AGA with less side effects needs to be found.

Traditional Tibetan medicine (TTM) is a long-established system of traditional medicine with a history of more than 2000 years and is formed based on the beliefs and practices of the Tibetan culture [16]. TTM consists of numerous botanicals, animal medicines, and mineral medicines, in which many medicines are unique because of the unique growth environment [17]. TTM belongs to traditional minority medicine in China and plays an important role in the health care system in Tibet Autonomous Region and other Tibetan regions such as Qinghai and Sichuan Provinces in China [16]. Qingpeng ointment is a Tibetan patent medicine for external use, which is convenient and safe to use. Only a few patients who are allergic to the drug may experience skin irritation after using the drug. Qingpeng ointment consists of *Herba Oxytropis Falcatae* (Jidou), *Rhei Spiciforme Randix* (Yadahuang), *Radix Aconiti Flavi Et Penduli* (Tiebangchui), *Chebulae Fructus* (Hezi), *Terminaliae Belliricae Fructus* (Maohezi), *Phyllanthi Fructus* (Yuganzi), *Benzoinum* (Anxixiang), *Caulis Tinosporae* (Kuanjinteng), and artificial *Moschus* (Shexiang). Qingpeng ointment has the effects of promoting blood circulation, removing blood stasis, reducing swelling, and relieving pain and can be used to treat swelling and pain of joint and muscle caused by rheumatic arthritis, rheumatoid arthritis, osteoarthritis, and gout. Previous clinical studies indicates that Qingpeng ointment can relieve pain, swelling, redness, and dysfunction of joints in patients with AGA [18–23]; can relieve joint pain and swelling in patients with knee osteoarthritis [24, 25]; and can relieve joint swelling in patients with rheumatoid arthritis [26]. However, previous studies of Qingpeng ointment for AGA have some methodological deficiencies. In order to clearly evaluate the efficacy and safety of Qingpeng ointment for patients with AGA, it is necessary to design and conduct a randomized controlled trial with higher methodological quality.

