### Study process

#### Baseline visit

After signing an informed consent, patients will be interviewed to obtain information on demographic characteristics, history of past and present illness, and current medications. General physical examination (including height, weight, blood pressure, respiratory rate, heart rate, and temperature) and laboratory tests (including serum uric acid and C-reactive protein) will be conducted. Degree of joint pain, swelling, redness, and mobility will be scored, and width and thickness of affected joints will be measured. Patients who meet the eligibility criteria will be randomly assigned to treatment group and control group, with 103 patients in each group. Investigators will also instruct participants on how to score the degree of joint pain, swelling, redness and mobility, and how to measure the width and thickness of joints.

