#### Treatment period

Patients in the treatment group will be treated with Qingpeng ointment, and patients in the control group will be treated with placebo ointment. Patients in both groups will be given diclofenac sodium sustained-release tablets (DSSRT) as rescue medicine. Drugs for other underlying diseases such as antihypertensive drugs, hypoglycemic drugs, and hypolipidemic drugs are permitted to be taken during the treatment period. And other Chinese patent medicine are prohibited during the trial. When participants experience severe skin allergies at application site, or experience serious adverse events, investigators will advise them to discontinue using the study drug. The degree of joint pain, swelling, redness, and mobility will be scored and recorded on patient diary every day by patients, and the width and thickness of affected joints will also be measured and recorded every day by themselves. The course of treatment is seven days.

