#### Treatment visit

After 7 days of treatment, participants will return to hospital for treatment visit. General physical examination and laboratory tests (including serum uric acid, C-reactive protein) will be conducted. The degree of joint pain, swelling, redness, and mobility will be scored, and the width and thickness of affected joints will be measured. The combined medication and adverse events during treatment period will be recorded. The remaining study drugs will be recovered, drug distribution and recovery record form will be filled in, and the remaining amount of Qingpeng ointment/placebo ointment and rescue medicine will be recorded.

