#### Rescue medicine

DSSRT (produced by Beijing Novartis Pharmaceutical Co., Ltd; specification: 75mg/tablet, 10 tablets/box) will be given to participants in both treatment group and control group as rescue medicine. Patients in both groups are recommended to take the rescue medicine only when the VAS score of joint pain is ≥ 7 points (scale of 0 to 10), which is scored by patients themselves. Patients will also be recommended not to take the rescue medicine when joint pain is reduced to a tolerable extent (VAS score reduce to less than 7 points). The recommended dose is one tablet per time, once daily, and the maximum dose is one tablet per time, twice a day.

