#### Allocation concealment and blinding

Sequentially numbered drug containers of identical appearance were used to achieve allocation concealment. Two hundred and six drug boxes with identical appearance were numbered as 001–206. According to the random sequence, Qingpeng ointment and placebo ointment were put into the corresponding numbered boxes, with three tubes of Qingpeng ointment or placebo ointment in each box. One box of DSSRT was also put into each drug box at the same time. Special personnel are assigned to manage the study drugs in each hospital, and the corresponding sequence of drugs will be distributed to each patient according to their recruitment sequence. Throughout the study, the investigators and the participants will not know which group the participants are assigned to. For each participant sequence, a corresponding emergency letter was made, which records the allocation result of that participant. When a participant experience serious adverse events and the allocation result needs to be known, investigators can open the emergency letter. The process of unblinding, including reasons, time, and treatment results, should be recorded on the case report form.

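### Every kit contains diclofenac, yet no exclusion covers ulcer, gastrointestinal bleeding or anticoagulant use, and no renal test is named to apply the kidney exclusion or detect a silent decline

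*Protocol article*

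**What the plan says.** All references are to the protocol article.

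- **Background.** "NSAIDs are associated with increased risk of gastrointestinal bleeding [13] and may exacerbate renal failure [14". The same section says that "comorbidities that may result in contraindications to these drugs are common in patients with gout".
- **Treatment period.** "Patients in both groups will be given diclofenac sodium sustained-release tablets (DSSRT) as rescue medicine". Medicines for other underlying diseases may continue; the only class prohibited there is other Chinese patent medicines.
- **Allocation concealment and blinding.** "One box of DSSRT was also put into each drug box at the same time". There are 206 drug boxes.
- **Rescue medicine.** Patients are "recommended to take the rescue medicine only when the VAS score of joint pain is ≥ 7 points", scored by themselves. One 75 mg tablet daily is recommended, and "the maximum dose is one tablet per time, twice a day". A box holds 10 tablets.
- **Exclusion criteria.** Diclofenac appears once, under allergy. Kidney disease excludes a patient only at the severe level, as do liver, cardiovascular and cerebrovascular disease. No gastrointestinal criterion and no anticoagulant criterion is listed.
- **Baseline visit.** Staff collect "history of past and present illness, and current medications". The laboratory tests are introduced as including uric acid and C-reactive protein.
- **Treatment visit (day 7).** "General physical examination and laboratory tests (including serum uric acid, C-reactive protein) will be conducted".
- **Safety outcomes.** Vital signs, examination findings and adverse events.

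**The concern.** The article justifies a topical treatment partly by the harms of NSAIDs and by how often gout patients have reasons not to take them. It then supplies an NSAID to everyone for use at home, and its eligibility list does not reflect the two harms it has just named.

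As written, a patient with a past ulcer bleed, a patient on an anticoagulant, or a patient with moderate renal impairment can be enrolled and sent home with diclofenac. The kidney exclusion is difficult to apply to someone whose disease is not already known, because no named test measures renal function. If renal function fell during the week without symptoms, nothing listed would show it. What is at stake is avoidable risk to participants and an incomplete safety record for a drug supplied by the trial.

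**Working it through.** The plan states no figure on this point, so the check compares sections of the article. The only arithmetic is exposure.

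**1. Exposure to diclofenac**

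Inputs: 75 mg per tablet, 10 tablets per box, recommended one tablet daily, maximum two daily, 7 treatment days (Rescue medicine; Treatment period).

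- Maximum daily dose: 2 x 75 mg = 150 mg.
- Total supplied: 10 x 75 mg = 750 mg.
- At the maximum dose the box lasts 10 / 2 = 5 of the 7 days.
- At the recommended dose 7 tablets are used: 7 x 75 mg = 525 mg, with 3 tablets left.
- Kits with diclofenac: 206 of 206. This counts supply, not use.

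Use is clearly expected. The inclusion criteria set a minimum pain score of 3 and no maximum, so a patient who enters at 7 or above may start on day 1. The Discussion anticipates very severe pain, and the amount of rescue medicine remaining is a secondary outcome.

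**2. Bleeding risk: named harm against safeguard**

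| Step | What the article provides |
|---|---|
| Harm named | Gastrointestinal bleeding (Background) |
| Exclusion | None for ulcer, previous bleed or anticoagulant use |
| Co-medication rule | Medicines for other conditions allowed; anticoagulants not barred |
| History at baseline | Taken, but no listed criterion acts on a bleeding history |
| Advice on when not to take diclofenac | Based on the pain score only |
| Detection | Adverse event reporting, which would capture an overt bleed |

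**3. Renal risk: named harm against safeguard**

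| Step | What the article provides |
|---|---|
| Harm named | Worsening of renal failure (Background) |
| Exclusion | Severe kidney disease only; mild or moderate impairment is eligible |
| Test to apply the exclusion | 0 of the 2 named baseline tests measures renal function |
| Test during or after use | 0 of the 2 named day-7 tests measures renal function |
| Safety outcome | No renal measure listed |
| Detection | Overt renal failure would be an adverse event; a symptomless fall would not be seen in vital signs, examination or patient report |

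**4. What each gap depends on**

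The bleeding gap follows from the exclusion list and the co-medication rule alone. The renal eligibility gap, that non-severe impairment is allowed, also follows from the exclusion list alone. Only the absence of a renal test depends on how the open laboratory list is read. The two tests it names are exactly the two laboratory measures among the secondary outcomes, so the article gives no sign of a separate safety panel, but it does not rule one out.

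**The case against.** The case on the other side has real force.

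- **The laboratory list is open.** Both visits describe the tests as including the two named, and a journal article condenses a fuller protocol. A routine panel with creatinine may already be run. This stands: one can say only that no renal test is named. It does not touch the eligibility gaps.
- **There is screening and monitoring.** Severe kidney disease is excluded, age is capped at 65, and history and medications are taken. Adverse events are recorded through treatment and a further 7 days. Serious events lead to advice to stop the study drug, and the allocation can be unblinded if needed. A reader might infer from the gaps that neither risk is screened or monitored at all; the article does not support that. What remains is that no criterion acts on a bleeding history and no named measure would reveal a silent renal change.
- **Supply is not use.** Diclofenac is conditional rescue, recommended once daily, in a condition for which the Background says NSAIDs are recommended first-line treatment. This stands, and exposure should not be described as universal.
- **Changing it has a cost.** Kits are packed and recruitment was under way, so an amendment must go to the ethics committee of each centre and to the registry. This is true but modest.

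A reader might also infer two things about interpretation. One is that the trial cannot show a reduction in NSAID harm; but the Objectives set no such aim, and both arms have the same rescue. The other is that impaired renal clearance would distort the uric acid comparison; but allocation is randomised, so baseline renal function is not expected to differ systematically between arms, and nothing in the article shows a bias.

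**Conclusion.** The point holds as a specific patient-safety gap in content the protocol article itself sets out. Eligibility and rescue rules are not matters left to a statistical analysis plan. Patients with a previous ulcer or bleed, patients on anticoagulants and patients with non-severe renal impairment are eligible as written and receive up to 150 mg a day of self-triggered diclofenac. In addition, no renal test is named to apply the kidney exclusion or to detect a symptomless decline.

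The size can be given only as supply: 206 of 206 kits, with 750 mg in each. A reader may want the number of vulnerable patients exposed, but the article gives neither the prevalence of these conditions in its population nor an expected rate of rescue use, so no such number can be supported.

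The conclusion on eligibility assumes that the printed exclusion list is complete. The conclusion on renal testing assumes also that creatinine is not already in the panel. If it is, the renal part reduces to stating how the value is used and listing it as a safety outcome. The gap should be corrected because the article identifies the risks itself and closing it is cheap. It does not affect the validity of the efficacy comparison.

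**What to change.** 1. **Exclusion criteria.** Add active or previous peptic ulcer or gastrointestinal bleeding, and current anticoagulant use. Alternatively, keep these patients eligible but bar them from diclofenac in the Rescue medicine section. In that case the diclofenac box has to be taken out of their kit, and the clinical team has to say what they may use for severe pain.
2. **Kidney criterion.** Measure serum creatinine in the baseline blood sample already drawn for uric acid and C-reactive protein, if it is not already measured, and use the result to apply the criterion. The threshold is a clinical decision; the article gives none.
3. **Day 7.** Measure creatinine again in the blood already drawn at the treatment visit.
4. **Safety outcomes.** List change in creatinine, gastrointestinal events and renal events.

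Cost: one routine assay at two visits, an amendment to each centre's ethics committee and the registry, and a few more screen failures. No extra visit or blood draw is needed. Waiting for the baseline result could delay treatment of an acute flare, so turnaround at each hospital should be checked before the rule is fixed.

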## Objectives

The aim of this study is to design and conduct a double-blind, randomized, placebo-controlled trial, to evaluate the efficacy and safety of Qingpeng ointment for AGA. The primary objective is to evaluate the efficacy of Qingpeng ointment in relieving the joint pain and reducing the joint swelling of patients with AGA. The secondary objectives are to evaluate the efficacy of Qingpeng ointment in improving the joint mobility and relieving the joint redness in patients with AGA, and to evaluate the safety of Qingpeng ointment.

## Methods

### Study design

This study is a prospective, multi-center, randomized, double-blind, placebo-controlled trial. The study protocol was written in accordance with the Standard Protocol Items: Recommendations for Interventional Trials (SPIRIT) guidelines (Additional file 1 shows the SPIRIT checklist). The trial has been registered on ISRCTN registry: www.isrctn.com. The flowchart of the study design is shown in Fig. 1, and a detailed schedule of enrolment, intervention, and assessment is shown in Fig. 2.

**Fig. 1 Fig1:**
[figure not shown]
Trial flow chart

**Fig. 2 Fig2:**
[figure not shown]
SPIRIT figure. Schedule of enrolment, interventions, and assessments

### Study setting

This study will be conducted in three hospitals: Fangshan Hospital, Beijing University of Chinese Medicine in Beijing; the Second Affiliated Hospital of Zhejiang Chinese Medical University in Hangzhou, Zhejiang Province; and Liuzhou People’s Hospital in Liuzhou, Guangxi Zhuang Autonomous Region.

### Study process

#### Baseline visit

After signing an informed consent, patients will be interviewed to obtain information on demographic characteristics, history of past and present illness, and current medications. General physical examination (including height, weight, blood pressure, respiratory rate, heart rate, and temperature) and laboratory tests (including serum uric acid and C-reactive protein) will be conducted. Degree of joint pain, swelling, redness, and mobility will be scored, and width and thickness of affected joints will be measured. Patients who meet the eligibility criteria will be randomly assigned to treatment group and control group, with 103 patients in each group. Investigators will also instruct participants on how to score the degree of joint pain, swelling, redness and mobility, and how to measure the width and thickness of joints.

#### Treatment period

Patients in the treatment group will be treated with Qingpeng ointment, and patients in the control group will be treated with placebo ointment. Patients in both groups will be given diclofenac sodium sustained-release tablets (DSSRT) as rescue medicine. Drugs for other underlying diseases such as antihypertensive drugs, hypoglycemic drugs, and hypolipidemic drugs are permitted to be taken during the treatment period. And other Chinese patent medicine are prohibited during the trial. When participants experience severe skin allergies at application site, or experience serious adverse events, investigators will advise them to discontinue using the study drug. The degree of joint pain, swelling, redness, and mobility will be scored and recorded on patient diary every day by patients, and the width and thickness of affected joints will also be measured and recorded every day by themselves. The course of treatment is seven days.

#### Treatment visit

After 7 days of treatment, participants will return to hospital for treatment visit. General physical examination and laboratory tests (including serum uric acid, C-reactive protein) will be conducted. The degree of joint pain, swelling, redness, and mobility will be scored, and the width and thickness of affected joints will be measured. The combined medication and adverse events during treatment period will be recorded. The remaining study drugs will be recovered, drug distribution and recovery record form will be filled in, and the remaining amount of Qingpeng ointment/placebo ointment and rescue medicine will be recorded.

